##### Analysis methods to handle protocol nonadherence and missing data 

We will adopt intention-to-treat analyses and imputation methods for missing data.

##### Interim analyses

A data analyst masked to intervention allocation will conduct interim analyses.

#### Qualitative data

We will use NVivo 12 (QSR International) for qualitative data analyses. Data from KIIs, IDIs, and FGDs will be analyzed thematically using both inductive and deductive coding [42]. We will adhere to the six phases of reflexive thematic analysis outlined by Braun and Clarke [43–45]. Preceding the analysis, the transcribed and translated data will be de-identified and rigorously cleaned for translation accuracy, a process verified by bilingual study team members using the original interview audio recordings. Beginning with the first phase, we will immerse ourselves in the data by thorough and repeated readings. Moving to the second phase, the team will tag pertinent features related to our research questions, assigning code labels. The codebook will take shape through an inductive and deductive approach, informed by topic guides and research questions, and coders will apply it to all transcripts, introducing and discussing new codes as needed. For the third phase, we will review and cluster similar codes to uncover patterns of shared meaning, potentially employing visual tools for organization. Subsequently, in the fourth phase, we will systematically review and discuss these patterns for each data segment and the dataset as a whole. In the fifth phase, we will refine emerging themes through thorough discussion, ensuring precise definition and nomenclature. Finally, in the last phase, the analysis will culminate in comprehensive written documentation of the final analysis findings.

#### Cost-effectiveness analysis

We will perform an economic evaluation following the principles, methodological specifications, and reporting standards recommended by the *International Decision Support Initiative Reference Case for Economic Evaluation (iDSI Reference Case)* [46]. Health benefits and costs will be measured from the societal perspective to consider the impact on the program, health system, and patient levels. Using a bottom-up costing approach, we will estimate the recurrent and fixed costs, including manpower (e.g., staff salaries), capital (e.g., equipment), other operating costs (e.g., consumables), and overheads. Considering the depreciation and opportunity costs, capital costs will be annualized over the product’s expected lifespan.

Program costs will include costs related to the intervention development, such as VHSG training and software development, based on the financial records of the implementing teams (UHS and NUS-SSHSPH). Research costs will be recorded but not included in the analyses as it has no implications on adopting the intervention in the real world. Health system costs will consist of the costs of providing preventive and curative MCH services at public health facilities based on WHO-CHOICE estimates and verified by PHDs. We will include items not included in the program but likely required if the intervention is adopted by the health system, such as the costs of integrating the intervention into the health system. The costs of digital integration will be based on consultations with the technology provider (Argusoft) and government officials with knowledge of digital infrastructure. We will consider the existing digital infrastructure required to support the intervention sunk-in costs and exclude them from the analyses.

We will estimate patient costs based on out-of-pocket expenditures reported by patients in the household surveys, including health and non-health costs for treatment of pregnancy complications and newborn and infant illnesses, ANC, delivery, and PNC in the public health system. Costing will only include expenditures incurred in the public health system to understand cost implications on the national healthcare budget. We will use data on service utilization from the household surveys and the registration information collected by the surveillance team, birth and death registration record, and, where possible, aggregate data provided by NMCHC in addition to public health system costs and out-of-pocket expenditures to estimate a standardized unit cost of delivering preventive and curative MCH services in the intervention and control arms.

We will conduct the economic evaluation using a cost-effectiveness analysis (CEA) by estimating the incremental costs and benefits of the intervention compared to the control, summarized in the incremental cost-effectiveness ratio (ICER). Decision-analytic modeling will be performed to estimate the cost per infant and maternal death averted, years of life saved (YLS) by averting an infant or maternal death, illness episode prevented, and disability-adjusted life years (DALY) averted between intervention and control. The incremental cost is the cost of integrating and using the intervention in the public health care system and the additional utilization of MCH services arising from the intervention.

The modeling will be based on improving service utilization, thereby reducing illnesses or complications during pregnancy and after birth and reducing maternal, neonatal, and child mortality. The reduction in mortality leads to a reduction in the years of life lost (YLL) due to premature mortality and a decrease in DALY. We will use disability weights in the Global Burden of Disease 2019 to compute years lived with disability (YLD) due to maternal complications and neonatal and infant illnesses. We will develop the model based on the evidence of preventive and curative services shown in the literature [47, 48] and the LiST (Lives Saved Tool) model [49]. The modeling will explore different time horizons, factoring in the downstream costs and benefits at varying intervention effects and when scaled up to more provinces and the national level.

We will employ a 3% discount rate for both costs and benefits, and sensitivity analyses will be done using different discount rates to account for uncertainty. In the absence of a local cost-effectiveness threshold (CET) for Cambodia, a less than one-time gross domestic product (GDP) per capita will be considered as “very cost-effective,” and between one to three times of GDP per capita will be regarded as “cost-effective” [50]. We will adapt the Consolidated Health Economic Evaluation Reporting Standards (CHEERS) checklist to report the cost-effectiveness outcomes. We will capture the aforementioned economic plans in a health economic analysis plan in consultation with the NMCHC and other stakeholders, such as WHO, through KIIs with personnel with expertise or knowledge in health financing or health technology assessments (HTA). The KII will cover the HTA process and requirements, including the goals and types of economic evaluations. As Cambodia does not have a national HTA organization or formal HTA policies and procedures, the consultation and KIIs will engage MOH in the financial evaluation process and, more broadly, about HTA. The KIIs will be conducted in phase 1 as part of the gap analysis.

Through the KIIs, we will engage with the MOH to share and engage government stakeholders in the economic evaluation. The KIIs will be conducted at baseline and endline as part of the qualitative evaluation. At the baseline, one KII will be conducted with regional partners (WHO and UNFPA) to understand best practices for HTA, and another KII will be done with NMCHC to understand if there is any HTA process and requirements in Cambodia, including preferred approaches for HTA. The interview data will help refine the economic evaluation methodology. At the endline, we will conduct a sharing session with NMCHC and other stakeholders to share the study findings and hear their views on how economic evaluation can feed into policymaking and shape the process for HTA establishment in Cambodia.

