**Methods:**

i-MoMCARE, a two-arm cluster randomized controlled trial, will be conducted between 2022 and 2025. Five operational districts (ODs) have been randomized to an intervention arm and the other five ODs to the control arm. The intervention will last for 24 months. Around 200 VHSGs in the intervention arm will be equipped with a mobile application as a job aid and 20 HC staff with a web interface to improve support and supervision of VHSGs. The potential beneficiaries will include pregnant women, mothers, and children under 2 years old. We will measure the outcomes at baseline and endline. The primary outcomes will consist of a composite MCH index constructed from maternal and newborn care indicators, child immunization, and treatment of under-two children. Secondary outcomes will include coverage of selected MCH services. We will conduct the intention-to-treat and per-protocol analyses. We will conduct qualitative interviews with selected beneficiaries and stakeholders to evaluate the intervention’s acceptability, feasibility, and scalability. We will also conduct a cost-effective analysis using decision-analytic modeling incorporating a societal perspective that explores different time horizons, intervention effects, and when scaled up to the national level.

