APNC will consist of four sub-components: (1) the proportion of mothers visited by VHSGs at least three times in the last pregnancy, (2) the proportion of mothers with at least four ANC visits in the last pregnancy and one tetanus vaccine injection, (3) the proportion of mothers delivered at a health facility (public or private), and (4) the proportion of mothers with at least three PNC visits in the last pregnancy. IMMU will consist of two sub-components: (1) the proportion of young infants aged 12–24 months fully vaccinated based on the national guideline with one dose of Bacillus Calmette–Guérin (BCG) vaccine for tuberculosis; three doses of polio vaccine given as oral polio vaccine (OPV), inactivated polio vaccine (IPV), or combination of OPV and IPV; three doses of diphtheria, pertussis, and tetanus (DPT) vaccine; and one dose of measles vaccine given as measles-rubella (MR) and (2) the proportion of young infants exclusively breastfed in the first 6 months. TREAT will consist of three sub-components: (1) the proportion of neonates with complications in the first month of the last delivery who seek care from VHSGs, (2) the proportion of infants aged two to 24 months with diarrhea in the last 2 weeks and receiving oral rehydration therapy (ORT) from VHSGs, and (3) the proportion of infants aged 2 to 24 months with acute respiratory infections in the last 2 weeks and seeking care from VHSGs.

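### The economic evaluation is labelled societal, but its costing stops at the public health system and still includes patients' own spending, so the ratio is neither societal nor a government-budget ratio

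*Protocol article*

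**What the plan says.** The abstract (Methods) promises "decision-analytic modeling incorporating a societal perspective". The Cost-effectiveness analysis section opens in the same way: "Health benefits and costs will be measured from the societal perspective to consider the impact on the program, health system, and patient levels".

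The costing rules that follow are narrower:

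- On the provider side: "Health system costs will consist of the costs of providing preventive and curative MCH services at public health facilities".
- On the patient side: "We will estimate patient costs based on out-of-pocket expenditures reported by patients in the household surveys, including health and non-health costs". That sentence goes on to confine these costs to care in the public system.
- As a general rule, with its reason: "Costing will only include expenditures incurred in the public health system to understand cost implications on the national healthcare budget".
- For the numerator of the ratio: "The incremental cost is the cost of integrating and using the intervention in the public health care system and the additional utilization of MCH services". No sector is named for the additional use.

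The effects are infant and maternal deaths averted, years of life saved, illness episodes prevented and DALYs averted. They are modelled from improved service utilization, again with no sector named. The ratio is judged against one and three times GDP per capita. The only cost-effectiveness sensitivity analysis named concerns the discount rate; the model will also vary time horizon, effect size and scale. No analysis from a second perspective is described.

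**The concern.** A societal perspective counts costs whoever bears them, so what a family pays a private midwife or clinic belongs in it. A government-budget perspective counts what the state pays, so what a family pays from its own pocket does not belong in it, even at a public facility. The plan leaves out the first and keeps the second. A reader of the result would not know which decision the ratio informs.

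This matters because the seventh specific objective is to evaluate cost-effectiveness for adoption and scale-up in Cambodia. A ministry reading a societal ratio would assume that a change in household spending on private care had been counted. A ministry reading a budget ratio would assume that household spending had been left out. Both would be wrong.

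**Working it through.** The protocol gives no ICER, unit cost or private-sector share, so there is no stated figure to reproduce. The check compares scopes, followed by an illustration on assumed inputs.

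**Step 1. Set the scopes side by side.**

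| Cost item | Societal | Government budget | Counted in the plan |
|---|---|---|---|
| Services at public facilities | yes | yes | yes |
| Out-of-pocket health and non-health costs, public system | yes | no | yes |
| Spending at private providers | yes | no | no |

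The last column matches neither perspective. It differs from the societal column in the third row and from the budget column in the second.

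**Step 2. Look for a passage that reconciles them.** The gloss on the perspective (program, health system and patient levels) does not, because payments to private providers are also a patient-level cost. The general rule sits in the paragraph on patient costs and could be read as governing those alone. That changes nothing, since provider-side costs are separately confined to public facilities. The health economic analysis plan announced in the same section is to capture the plans already described, so it would inherit the conflict.

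**Step 3. Compare with the effect side.** The modelled effects follow from service use, and no sentence confines that use to public facilities. Costs and effects may therefore cover different care. The text goes no further than that.

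**Step 4. Illustrate the possible size (all inputs assumed).** Only between-arm differences enter an ICER. Private spending that is the same in both arms cancels, and the error is then zero. Two cases where it does not cancel:

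*Private use rises.* Let w be the share of incremental cost due to extra service use when all of it is priced at the public unit cost, s the private share of that extra use, and r the private-to-public unit-cost ratio. Then

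public-only / full cost = [(1 − w) + w(1 − s)] / [(1 − w) + w((1 − s) + s·r)].

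- w = 0.3, s = 0.1, r = 1: (0.70 + 0.27) / (0.70 + 0.30) = 0.97.
- w = 0.6, s = 0.4, r = 2: (0.40 + 0.36) / (0.40 + 0.84) = 0.76 / 1.24 = 0.61.

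With the modelled benefit held fixed, the ICER would be too low by about 3% to 39%.

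*Users move from private to public care, with no net extra use.* Public-only incremental cost is (1 − w) + w = 1.0. Societal incremental cost is 1 − w·r.

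- w = 0.3, r = 1: 1 − 0.3 = 0.7.
- w = 0.6, r = 2: 1 − 1.2 = −0.2.

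Here public-only costing makes the ICER too high, and at the extreme it hides a net saving. The sign depends on the direction in which use shifts, and the protocol does not give this.

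**The case against.** The strongest reply is that the restriction is stated openly with its reason, and that the protocol explains what it means by societal. It does count patient costs, so calling the costing a pure payer view would be wrong. On this reading only a label is too broad. Much of this stands: a careful reader can see what is costed. But the label and the rule are both in the text, they conflict, and the budget reason does not fit the patient costs that are kept.

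A reader might go further and infer that the ratio credits private-facility care as benefit while leaving its cost out. The documents do not support that as a fact. The wording that counts delivery in either sector ("the proportion of mothers delivered at a health facility (public or private") belongs to the trial's coverage index, which is not a denominator of the ICER. The household-survey utilization data are mentioned in connection with a standardized unit cost. No sentence says that private use enters the model, and none says that it does not.

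A reader might also take the private share of all patient spending as the size of the error. That is a share of total cost, whereas the ICER depends on incremental cost. A rise in private use also fits the design less well than a shift to public care, since the volunteers refer women and children to the nearest health center. That makes one direction more plausible without settling it.

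Finally, the GDP thresholds are not tied to any perspective in the text, so their use is not a separate error. Further scenario analyses may properly be left to the health economic analysis plan; their absence from an article is not a defect.

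**Conclusion.** The point holds as a contradiction between the declared perspective and the costing rule. As written, the ICER is neither societal nor a government-budget ratio. This rests on the text alone and needs no assumption.

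A mismatch between the care that is costed and the care that produces the modelled benefit is possible but not shown. Neither the size nor the direction of bias can be derived from the protocol. The 0.97 to 0.61 range, and the reversal under substitution, rest wholly on the assumed w, s and r and on benefits being held fixed; they show only that the omission need not be negligible. The trial's effectiveness analyses are untouched. What is affected is the interpretation of the cost-effectiveness objective, so this should be corrected but does not threaten the trial.

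**What to change.** 1. In the societal base case, include out-of-pocket health and non-health spending at private as well as public providers, taken from the household survey. The Household survey section already lists health expenditures among the items collected.
2. Report the public-only costing as a second analysis, labelled as a health-system or budget analysis. Leave out-of-pocket costs out of any budget analysis.
3. If spending by provider type was not recorded, relabel the perspective in the abstract and at the opening of the Cost-effectiveness analysis section as public health system plus public-sector patient costs, and state the omission of private costs as a limitation.
4. Do not restrict the health effects to public facilities to match the costs. A woman who moves from a private to a public facility would then count as a new health gain although she would have received facility care anyway.
5. State whether the utilization that drives the model covers both sectors.

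The cost is a few sentences and a modest amount of extra analysis. Whether the questionnaire records provider type cannot be seen from the article. If it does not, one field is needed in the expenditure questions; a field added only at endline would have no baseline counterpart, and that should be said when the result is reported.

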### Oversight and monitoring

#### Composition of the coordinating center and trial steering committee

The coordinating center will be based at UHS, the primary implementing organization. The steering committee will comprise representatives of NMCHC, NUS-SSHSPH, UHS, and key stakeholders working on MCH in Cambodia (e.g., WHO, UNICEF, UNFPA, USAID, and local NGOs). Data will be stored and managed by the team at UHS, with technical support from NUS-SSHSPH and Argusoft. The research team from NUS-SSHSPH will be responsible for data analyses. The steering committee will adjudicate the endpoints and develop the findings dissemination plan in consultation with the data monitoring committee. During the trial preparation phase, the steering committee will meet every month, and during the intervention, the committee will meet every quarter (or ad hoc meeting). The research team will produce meeting reports to update research progress or report any issues during the project implementation.

#### Composition of the data monitoring committee and the reporting structure

The data monitoring committee (DMC) will comprise Argusoft, NUS, and UHS representatives. We will form the DMC independently from the funders. The committee members are not directly involved in the project; however, they are affiliated with organizations within the project consortium (UHS and NUS) and the technical support firm (Argusoft). The DMC will be responsible for independently assessing the integrity and validity of the RCT. We will present the interim analyses to the DMC. The DMC will report the trial progress and results to the steering committee. The DMC will meet twice a year or as needed.

#### Adverse event reporting and harms

The study will impose no major perceivable risks, and the potential psychological distress in the interviews will be minimal. Participation is voluntary, and the decision to decline or discontinue this study at any time during the study will not have any negative consequences. All participants and those who refuse to participate in the survey will receive standard MCH care.

#### Plans for auditing trial conduct

We plan to conduct at least four monitoring visits to each operational district during implementation. Field supervisors will conduct at least eight monitoring visits (e.g., every quarter). During monitoring visits, we will review consent forms, completeness of the data collection forms, compliance with the trial protocol, and follow up on any anomalies in recruitment and data. The research team will monitor data, recruitment processes, and interim results and report to the DMC.

#### Plans for communicating significant protocol amendments

We will communicate amendments to the protocol to all relevant parties, including trial participants and ethical committees, the NMCHC and all partners, investigators, ethics boards in Cambodia and Singapore, the trial registry, and journals.

#### Dissemination plans

We will share the study findings in dissemination workshops with key stakeholders and in peer-reviewed journals. Following the International Committee of Medical Journal Editors guidelines, we will determine authorship credit based on the research team members’ contribution to the conception, design, execution, or analysis and interpretation of the data. All authors should be involved in drafting the article or revising it critically for important intellectual content and must have read and approved the final version of the manuscript. We will publish information from the full protocol and tools in a peer-reviewed journal. The relevant data analyzed during the development of this study protocol are available upon request from the corresponding author.

##### Ethical considerations

The trial will follow the Good Clinical Practice guidelines [51]. We will amend and resubmit the study protocol to the aforementioned ethical committees if there are significant changes. At the beginning of each interview, participants will be informed about the study’s objectives, data confidentiality, the risks and benefits of their participation, the voluntary nature of the participation, and their rights to refuse or discontinue the study at any time. Additional file 4 provides patient information sheets and consent forms. Interviews will be conducted in settings that protect the participants’ privacy, and we will use study identification numbers instead of personal identifiers. Only the project staff from NUS-SSHSPH and UHS will have access to the personal data in the trial. We will not publish the data and discard them after disseminating the results.

